### Data extraction methods

Care providers using the eRegistry or the paper records will continuously enter data during patient care. All data from completed paper records (after delivery of the baby) from the control PHC are routinely computerized by trained registry staff into the eRegistry every month. Double data extraction is carried out on approximately 10% of all the paper-based files for quality assurance purposes. Birth outcome data from public hospital maternity wards and delivery units are collected independently by hospital staff using their routine health information system which is not automatically linked to the eRegistry. These data are routinely exported from the hospital health information system’s national server every month, and merged into the eRegistry using the unique identifiers of the mothers. Data on births from all other hospitals with maternity wards and delivery units, including private hospitals and those run by NGOs, are collected by the Palestinian MoH staff using a standardized form on a monthly basis, and also merged into the eRegistry. For this CRCT we will only use anonymous data extracted from the eRegistry in accordance with the SOP of the Palestinian maternal and child health eRegistry for routine registry operations and use of data for research purposes [26].

### Data management

The data in the eRegistry will be managed in accordance with the governance structure approved by the Palestinian MoH [26]. Only predefined anonymous data needed for the outcomes will be provided to the principal investigator, the trial manager in Palestine, and to CISMAC for independent monitoring and safeguarding of the original dataset for analyses.

### Statistical methods

Data will be analyzed using STATA version 14 or later (StataCorp. 2015. Stata Statistical Software: Release 14*.* College Station, TX, USA). Primary analyses will be according to intention-to-treat comparing control and intervention groups using individual-level data taking the design effect of the clustering into account. In addition, we will undertake a per-protocol analysis. A baseline table with summary measures for the following background characteristics of participants will be reported: maternal age, parity, average monthly household income, education, medical history, obstetrical history, body mass index, blood pressure at booking visit, hemoglobin at booking visit, urine stick results for glucose at booking visit, birth weight, and fetal presentation at term. We will first undertake a cluster-level analysis for the primary and secondary outcomes. We will then perform analyses on individual-level data. All primary outcomes of the study will be measured as proportions. Comparisons of categorical variables will use generalized estimating equations (GEE) with a log link. We will use two-sided statistical tests and 95% confidence intervals for descriptive statistics and effectiveness estimates. In order to take into account the inherent clustering in our trial design, we will use random effects models. The effect of the intervention on the risk and prevalence of outcomes will be reported as relative (risk ratios (RR) and prevalence ratios (PR)) and absolute (risk difference and prevalence difference) measures of effect. Effectiveness will be calculated as 100 × (1 – RR) and 100 × (1 – PR) as appropriate. We will consider adjusting for confounders if there are baseline imbalances in the trial arms for variables that are strongly associated with the primary outcomes. We will perform complete case analyses and consider appropriate imputations for missing data. We will employ spider graphs in order to graphically display the effect of the intervention and whether a disproportionately large part of the effect can be ascribed to extreme effects in a few large clusters. In the rare event of protocol violations such as withdrawal of the eRegistry from an intervention PHC, data from these clusters will be excluded for women enrolled from the time of violation and onwards. All data on the pregnant women who maintain allocation, irrespective of from which cluster they receive care, will be included in the analyses. For those women that switch from intervention to control PHC, they will be analyzed as randomized in the primary, intention-to-treat analyses. In the per-protocol analysis, only data prior to switching clinics will be used and the rest will be treated as missing data. We will undertake instrumental variable analyses to better estimate the field efficacy of the intervention, in anticipation of possible nonadherence to the intervention [30]. For this analysis, the random allocation to the two arms of the CRCT will be the instrument. To enable this analysis, we will capture backdated data entry into the eRegistry from paper back-up (provided for use in cases of power outages and internet disruptions) to assess actual receipt of the intervention by the pregnant women. We will present additional analyses of quality of antenatal care measures in order to gain better understanding of the primary process (adherence) outcomes of the trial. These include: the proportion of women booked for care that both utilize and receive appropriate care; the probability of a woman affected by pregnancy complications to be successfully identified and managed; and provider-centric performance (the proportion of visits in which timely and appropriate care is provided).

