### Outcomes

The focus of the outcome measures have been informed by national stakeholder consultations as representing key areas of quality concern in the Palestinian context, and to serve as sentinel outcomes for the overall quality of care. The adverse pregnancy outcomes reflect conditions that put the baby and/or mother at risk during labor or after delivery, and that could or should have been identified and/or managed prior to labor and delivery. The process (adherence) outcomes (Table 2) for the screening and management of the risk conditions and the corresponding adverse pregnancy outcomes (Table 3) will be assessed as primary outcomes. We have defined indicators to measure the process (adherence) outcomes (Additional file 1) based on the current guideline-based algorithms for management of conditions during ANC in Palestine (Additional file 2). Secondary outcomes are given in Table 4.

**Table 2 Tab2:** Primary process (adherence) outcomes, source of data, measurement sequence, and definitions

Process (adherence) outcomes	Source of data	Measurement sequence	Definitions
Timely and appropriate screening and management of anemia during pregnancy	Case records data from the PHC in the eRegistry	Registrations continuously at point of care, data export to the trial monthly	Proportion of women attending ANC who receive: 1. anemia screening at booking, and 2. screening at any ANC visits at 24 and 36 weeks if no anemia detected, and 3. rescreening after 1 month if mild or moderate anemia is detected, and 4. referred to high-risk clinic if refractory mild or moderate anemia is detected, and 5. referred to hospital if severe anemia is detected.
Timely and appropriate screening and management of hypertension in pregnancy	Case records data from the PHC in the eRegistry	Registrations continuously at point of care, data export to the trial monthly	Proportion of women attending ANC who receive: 1. blood pressure measurement at booking visit, and 2. blood pressure measurement at every ANC visit, and 3. appropriate laboratory tests for mild hypertension, and 4. referred to high-risk clinic hospital for chronic or gestational hypertension, and 5. referred to hospital for hypertension with proteinuria or signs of eclampsia.

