Timely and appropriate screening and management of abnormal fetal growth	Case records data from the PHC in the eRegistry	Registrations continuously at point of care, data export to the trial monthly	Proportion of women attending ANC who receive: 1. first fundal height measurement at 16–20 weeks, and 2. fetal growth monitoring at every ANC visit, and 3. referred to ultrasound if discrepancy between fundal height and gestational age, and 4. referred to high-risk clinic if ultrasound confirmed fetal growth restriction.
Timely and appropriate screening and management of diabetes in pregnancy	Case records data from the PHC in the eRegistry	Registrations continuously at point of care, data export to the trial monthly	Proportion of women attending ANC who receive: 1. diabetes screening at booking, and 2. screening with random blood sugar test at 24–28 weeks, and 3. referred to high-risk clinic if random blood sugar test or glucose challenge test ≥ 140 mg/dl.

*ANC* antenatal care, *eRegistry* electronic registry, *PHC* primary healthcare clinics

**Table 3 Tab3:** Primary adverse pregnancy outcomes, source of data, measurement sequence, and definitions

Adverse pregnancy outcomes	Source of data	Measurement sequence	Definitions
Moderate or severe anemia at admission for labor	Hemoglobin admission data from hospitals in the eRegistry (public, private, and NGO hospitals)	Registrations continuously at point of care, data export to the trial monthly	Moderate anemia: hemoglobin greater than 7 and less than 9 g/dl; severe anemia: hemoglobin < 7 g/dl
Severe hypertension at admission for labor	Blood pressure admission data from hospitals (public, private, and NGO hospitals) in the eRegistry	Registrations continuously at point of care, data export to the trial monthly	Severe hypertension: systolic blood pressure ≥ 160 mmHg and/ or diastolic blood pressure ≥ 110 mmHg
Malpresentation at delivery undetected during pregnancy	Presentation at delivery data from hospitals (public, private, and NGO hospitals) in MCH registry	Registrations continuously at point of care, data export to the trial monthly	All non-cephalic presentations at or after 36 weeks of gestation and at labor
Small-for-gestational age baby at delivery undetected during pregnancy	Birth weight data from hospitals (public, private, and NGO hospitals) in the eRegistry	Registrations continuously at point of care, data export to the trial monthly	Small for gestational age: less than 2549 g [34]

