Large for gestational age baby at delivery	Birth weight data from hospitals (public, private, and NGO hospitals) in the eRegistry	Registrations continuously at point of care, data export to the trial monthly	Large for gestational age: greater than 3980 g [34]

*eRegistry* electronic registry, *MCH *Maternal and Child Health, *NGO* nongovernmental organization

**Table 4 Tab4:** Secondary outcomes, source of data, measurement sequence, and definitions

Secondary outcomes	Source of data	Measurement sequence	Definitions
Timely ANC visits	Case records data from the PHC in the eRegistry	Registrations continuously at point of care, data export to the trial monthly	Proportion of women attending ANC who receive timely ANC visits according to guidelines at: 1. booking visit 2. 16 weeks gestation 3. 18–22 weeks gestation 4. 24–28 weeks gestation 5. 32 weeks gestation 6. 36 weeks gestation
Timely and appropriate screening and management of malpresentation ≥ 36 weeks	Case records data from the PHC in the eRegistry	Registrations continuously at point of care, data export to the trial monthly	Proportion of women attending ANC who receive: 1. screening for fetal presentation at any visit ≥ 36 weeks, and 2. referred to hospital for non-cephalic presentation
Stillbirth	Stillbirth data from the hospitals (public, private, and NGO hospitals) in the eRegistry	Registrations continuously at point of care, data export to the trial monthly	Baby born with no signs of life at or after 28 weeks of gestation

*ANC* antenatal care, *eRegistry* electronic registry, *NGO* nongovernmental organization, *PHC* primary healthcare clinics

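### Birth weight and fetal presentation at term are listed as baseline characteristics and left open to imbalance-triggered adjustment, although they follow exposure and feed three of five composite components

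*Protocol article*

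**What the plan says.** The Statistical methods section introduces its list in these words: "A baseline table with summary measures for the following background characteristics of participants will be reported". The list runs from maternal age and parity through booking-visit measurements and ends with "urine stick results for glucose at booking visit, birth weight, and fetal presentation at term". Later in the section comes the adjustment rule: "We will consider adjusting for confounders if there are baseline imbalances in the trial arms for variables that are strongly associated with the primary outcomes". No listed variable is excluded from that rule, and the section names no other set of baseline variables.

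Table 3 (Outcomes) takes the two birth-size components from "Birth weight data from hospitals (public, private, and NGO hospitals) in the eRegistry". The cut-offs are "Small for gestational age: less than 2549 g" and "Large for gestational age: greater than 3980 g". The malpresentation component is defined as "All non-cephalic presentations at or after 36 weeks of gestation and at labor". The small-for-gestational-age and malpresentation components count only cases undetected during pregnancy. The large-for-gestational-age component has no such condition.

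On timing, the Timeline section says intervention clinics had used the eRegistry exclusively for an average of 20 weeks before recruitment began, and that adverse pregnancy outcomes are captured over a further 8 months after the recruitment period.

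**The concern.** A baseline characteristic should be fixed before the intervention can act on it. Birth weight is known only at delivery, and presentation at term only at the end of pregnancy. By then the woman has had her antenatal care under the allocated system. A between-arm difference in either variable may be an effect of the intervention, and a baseline table would present it as a chance difference.

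The label matters because of the adjustment rule. Both variables are associated with the composite through its definition, so they readily meet the rule's second condition. If the intervention shifts either of them, the shift looks like imbalance and meets the first. An analyst could then condition the primary health outcome on part of itself and shrink a real effect. Coded allocation groups, as described under Blinding, do not prevent this, because a difference between two coded groups is visible without knowing which is the intervention.

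**Working it through.** The point rests on no figure that the plan reports, so there is none to reproduce. The check has three steps.

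**1. Are the variables pre-exposure?** No. Clusters were allocated and using the system before any trial woman enrolled, and both variables arise at the end of pregnancy. They are unlikely to be data from earlier pregnancies: obstetrical history is a separate item in the same list, and presentation is specified at term.

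**2. How much of the composite do they feed?** Control prevalences from Table 5:

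| Component | Prevalence | Uses birth weight or presentation? |
|---|---|---|
| Moderate or severe anemia | 0.0225 | no |
| Large for gestational age | 0.054 | yes, alone |
| Small for gestational age, undetected | 0.057 | yes, with non-detection |
| Malpresentation, undetected | 0.02 | yes, with non-detection |
| Severe hypertension | 0.01 | no |

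Sum = 0.1635. The three fed by these variables: 0.054 + 0.057 + 0.02 = 0.131, and 0.131 / 0.1635 = 0.80. (The plan's composite of 0.145 is below the sum because it allows for coexisting conditions. The sum is used here only for shares.)

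**3. What could adjustment do?** Assumptions of this illustration, not of the plan: components independent, except that a baby cannot be both small and large; no clustering; a 25% reduction (the lower end of the effect range in the Sample size section) in the components named; adjustment by a Mantel-Haenszel risk ratio stratified on birth-weight category and presentation.

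Control risk = 1 − (1 − 0.111)(1 − 0.02)(1 − 0.0225)(1 − 0.01) = 0.157.

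*Case A: all five components fall by 25%, through the conditions themselves, with the non-detection condition ignored.*
- Intervention risk = 1 − (1 − 0.08325)(1 − 0.015)(1 − 0.016875)(1 − 0.0075) = 0.119. Crude RR = 0.119 / 0.157 = 0.76.
- In every stratum with abnormal birth weight or presentation, the event is certain in both arms. These strata add the same amount, 0.0553, to the numerator and the denominator.
- In the remaining stratum, the risks from anemia and hypertension are 0.0242 (intervention) and 0.0323 (control), with weight 0.871 × 0.903 / (0.871 + 0.903) = 0.443. This adds 0.0108 and 0.0143.
- Adjusted RR = (0.0553 + 0.0108) / (0.0553 + 0.0143) = 0.95.

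*Case B: only the three birth-weight and presentation components fall by 25%, again with non-detection ignored.*
- Intervention risk = 1 − (0.91675)(0.985)(0.9775)(0.99) = 0.126. Crude RR = 0.126 / 0.157 = 0.80.
- Within every stratum the risks are equal, so the adjusted RR = 1.00.

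*Case C: undetected small-for-gestational-age and undetected malpresentation fall by 25% through better detection alone; birth weight and presentation do not change.*
- Intervention risk = 1 − (1 − 0.054 − 0.04275)(0.985)(0.9775)(0.99) = 0.139. Crude RR = 0.139 / 0.157 = 0.89.
- The strata are the same size in both arms, so the stratified RR equals the crude RR: 0.89. Nothing is lost.

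The loss therefore depends on the route of the effect: none in case C, most in case A, all in case B.

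**The case against.** The strongest reply is that the adjustment sentence does not refer to the baseline table. It comes several sentences later, speaks of confounders and baseline imbalances, and promises only to consider adjustment. A careful analyst would not call a component of the outcome a confounder. The primary analysis is an intention-to-treat comparison of arms, and covariate detail is commonly left to an analysis plan not shown here. Much of this stands. A reader might infer that the plan commits to adjusting for birth weight and presentation; the text does not say so. What remains is that the document itself calls both variables baseline characteristics, names no other baseline set in that section, and exempts neither.

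A second reply is that two of the three components also require non-detection, so the composite is not simply a function of birth weight and presentation. This stands in full. A reader might infer that adjustment must erase the effect whenever the intervention works. Case C shows otherwise: better detection can lower the composite with both variables balanced, and adjustment then does no harm. Cases A and B set the non-detection condition aside, so they show what is possible and do not estimate the loss for the composite as defined.

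Third, the four primary process outcomes are not defined by either variable. That is also correct, and the main point is confined to the composite. Booking hemoglobin and blood pressure are a lesser matter. They precede most antenatal care, and nothing in the plan proposes them as covariates for the process outcomes. But each measurement is itself the first item of a Table 2 outcome (for anemia, "1. anemia screening at booking, and 2. screening at any ANC visits at 24 and 36 weeks if no anemia detected"), so a missing value is already a failure of that outcome, and a complete-case model adjusted for it would drop such women. Imputation, which the plan also says it will consider, might soften this. It warrants a precaution only.

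**Conclusion.** The concern holds in a limited form. The misclassification is certain on the face of the document: two variables observed after exposure are called baseline characteristics, and they feed components that carry about 80% of the summed prevalence of the composite. The bias is possible, not certain. It needs the analysts to treat these variables as adjustment candidates, which the wording permits but does not require, and it needs some of the intervention's effect to act through birth weight or presentation. Under the stated assumptions, the attenuation ranges from none (0.89 stays 0.89) through most of the effect (0.76 becomes 0.95) to all of it (0.80 becomes 1.00). The documents give no basis for choosing a point in that range.

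**What to change.** 1. Take birth weight and fetal presentation at term out of the baseline table and report them by arm as delivery or outcome data.
2. State that neither is an adjustment covariate for any primary outcome.
3. Replace the imbalance-triggered rule with adjustment for covariates that the intervention cannot affect, fixed before unblinding and preferably before outcomes are tabulated by coded group. Suitable choices are the stratification and constraint variables in the Allocation section (district, annual new enrollments, laboratory availability, proportion of enrollments above 40 years of age, proportion of primiparous women), plus, for example, maternal age, parity and education.
4. As a precaution, keep booking hemoglobin and blood pressure descriptive, with their missingness by arm, and do not use them as covariates for the process outcomes whose first item is that same measurement.

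The cost is wording only. No new data are needed and the sample size does not change. If the analysis plan already fixes such a list, a sentence there excluding the two delivery variables and a corrected baseline table are enough.

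### The post-violation exclusion is not confined to the per-protocol analysis, so as written it contradicts the intention-to-treat primary analysis

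*Protocol article*

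**What the plan says.** All of the rules at issue stand in one paragraph of the protocol article, under Statistical methods.

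- Primary analysis set: "Primary analyses will be according to intention-to-treat comparing control and intervention groups using individual-level data".
- Second analysis set: "In addition, we will undertake a per-protocol analysis".
- Trigger for exclusion: "In the rare event of protocol violations such as withdrawal of the eRegistry from an intervention PHC".
- Consequence: "data from these clusters will be excluded for women enrolled from the time of violation and onwards".
- Inclusion sentence that follows: "All data on the pregnant women who maintain allocation, irrespective of from which cluster they receive care, will be included in the analyses".
- Switching, ITT: "For those women that switch from intervention to control PHC, they will be analyzed as randomized in the primary, intention-to-treat analyses".
- Switching, per-protocol: "In the per-protocol analysis, only data prior to switching clinics will be used and the rest will be treated as missing data".

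The same paragraph plans an instrumental variable analysis for non-adherence, with random allocation as the instrument. Elsewhere, Eligibility criteria says that all new enrolments in eligible clinics count towards the outcomes. Trial design makes the clinic, or a small group of clinics, the unit of randomisation. Intervention says that control clinics stay on paper for the whole trial.

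**The concern.** Under ITT, a woman enrolled at a randomised cluster belongs to that cluster's arm whatever later happens to the clinic. The exclusion rule removes her because of something that happened after randomisation, and nothing in the sentence limits it to the per-protocol analysis. The one trigger it names cannot occur in a control clinic, which has no eRegistry to withdraw.

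Three things are at stake.

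- **The question answered.** The objective is effectiveness in a pragmatic trial. Clinics that lose the system are part of that. Dropping their later enrolments removes the dilution they cause.
- **The instrumental variable analysis.** It relies on comparing the arms as allocated. If the rule applies to it as well, it discards women who were allocated to the intervention but did not receive it, and these are the women it exists to account for.
- **Selection.** If clinics that lose the system differ from the rest in underlying outcome level, removing their later enrolments from one arm unbalances the comparison.

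**Working it through.** **Reading the text.** The two rules on switching each name their analysis set. The exclusion rule names none, and the sentence after it speaks of the analyses in general. The authors therefore attached labels where they wanted to limit a rule. The plain reading is that the exclusion applies throughout, including the primary analysis, and that reading cannot stand beside the ITT declaration or Eligibility criteria.

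**Size.** The documents give no number of violating clusters, so what follows is a range of assumptions.

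Inputs from the documents: 120 clusters allocated 1:1 (about 60 per arm), mean cluster size 44, intracluster correlation 0.01 for adverse outcomes and 0.04 for process outcomes, coefficient of variation of cluster size 0.85 (Sample size, Allocation); control prevalence 0.145 for the composite (Table 5).

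Check of the plan's own figures: design effect = 1 + ((CV² + 1)m − 1) × ICC. With (0.7225 + 1) × 44 − 1 = 74.79, this gives 1 + 74.79 × 0.01 = 1.748 and 1 + 74.79 × 0.04 = 3.992. The stated 1.75 and 3.99 are reproduced, so the cluster inputs are read correctly.

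Assumption: 1, 3 or 6 of 60 average-sized intervention clusters are withdrawn from the first day, so the share of intervention women lost is f = 1/60, 0.05 or 0.10 (about 44, 132 or 264 of 2,640).

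*(a) Lost dilution.* Suppose the true risk ratio (RR) is 0.75 for the composite or 1.25 for a process outcome, and women enrolled after withdrawal get no effect. Then ITT RR = (1 − f) × RR + f, while the exclusion rule reports RR itself.

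*(b) Selection, no true effect, composite.* Suppose withdrawn clinics carry 1.5 times the risk of the others. Then 0.145 = (1 − f)a + 1.5fa, and RR after exclusion = a/0.145 = 1/(1 + 0.5f).

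*(c) Selection, no true effect, process outcome.* Suppose withdrawn clinics have half the average adherence. Then RR after exclusion = (1 − 0.5f)/(1 − f).

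| Clusters withdrawn | (a) composite: ITT vs excluded | (a) process: ITT vs excluded | (b) composite, true RR 1 | (c) process, true RR 1 |
|---|---|---|---|---|
| 1 | 0.754 vs 0.750 | 1.246 vs 1.250 | 0.992 | 1.008 |
| 3 | 0.762 vs 0.750 | 1.238 vs 1.250 | 0.976 | 1.026 |
| 6 | 0.775 vs 0.750 | 1.225 vs 1.250 | 0.952 | 1.056 |

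*Direction.* Reverse assumption (b), so that withdrawn clinics carry 1/1.5 of the others' risk. Then RR = 1/(1 − f/3). At f = 0.05 this is 1/0.9833 = 1.017, which goes against the intervention. The sign of the selection bias follows from the assumption. Under (a), by contrast, exclusion moves the estimate towards the intervention whenever there is a true benefit.

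**The case against.** The strongest reply is that the rule was meant for the per-protocol analysis, that the event is expected to be rare and use of the eRegistry is mandatory (Adherence), and that the effect on the result would be negligible. The last part largely stands: one average cluster withdrawn from the start moves RR by less than 0.01, against a planned relative change of 25–30% in the composite. The intended meaning may well be per-protocol, but the text does not say so. If violations occur, the choice between readings would be made after the fact.

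A reader might also infer four stronger things that the documents do not support.

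- *That the rule can act on one arm only.* Withdrawal is given as an example. A control clinic that received the eRegistry early would also depart from the plan, and Data monitoring foresees control clinics implementing it as soon as capacity allows. The one-arm point is exact only for the named trigger.
- *That it excludes clinics with power or internet failures.* It does not. Adherence provides replacement computers and back-up internet, and Statistical methods provides paper back-up with backdated entry and sends that non-adherence to the instrumental variable analysis.
- *That the resulting bias favours the intervention.* For selection, this needs withdrawn clinics to perform worse, which nothing in the documents shows.
- *That women moving from control to intervention clinics lose ITT protection.* The general ITT statement already covers them; naming one direction does not exclude the other.

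**Conclusion.** The point holds as an internal contradiction about who enters the primary analysis. As written, the rule is an exclusion based on post-randomisation events. It conflicts with ITT and with the counting of all new enrolments, and its only named trigger belongs to the intervention arm.

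The numerical consequence is probably small. Under the assumed inputs, one withdrawn cluster of about 60 shifts RR by about 0.004 through lost dilution or 0.008 through selection. Three to six clusters shift the composite by about 0.012 to 0.025 and 0.024 to 0.048 respectively, and selection on a process outcome reaches 0.056. These rest on withdrawal from the first day, average-sized clusters, no effect after withdrawal, and the chosen 1.5-fold risk or halved adherence. Later withdrawal gives smaller shifts. The documents supply none of these inputs, and they leave the direction of selection bias open. Only the loss of dilution has a predictable sign, in favour of the intervention when there is a true benefit.

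**What to change.** Before the allocation codes are released, reword the paragraph on three points.

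1. In the primary ITT analysis, every woman newly enrolled at a randomised cluster during recruitment is analysed in that cluster's allocated arm, whatever happens to the eRegistry there and whichever way she later switches.
2. The exclusion of women enrolled after a violation applies to the per-protocol analysis only, and the instrumental variable analysis keeps them.
3. Protocol violations are defined for both arms, including early receipt of the eRegistry by a control clinic.

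The cost is mostly wording, with two qualifications. First, Table 2 takes process outcomes from clinic records held in the eRegistry, and Data extraction methods describes computerising paper records for control clinics only. An intervention clinic that returns to paper would need that route extended to it, or its process data handled as missing. Composite outcomes arrive through the hospitals and are not affected in this way. Second, keeping diluted data costs some power. At a true composite RR of 0.75, with six clusters withdrawn from the start, a two-sided 5% comparison with the design effect above has about 76.4% power when these women are kept and 82.9% when they are dropped; with one cluster the figures are 83.7% and 84.6%. That loss is part of estimating effectiveness and does not justify the exclusion.
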